#### 2.5.2. Blood Sample Collection and Handling

Blood samples will be obtained via peripheral venepuncture or an existing intravenous line using aseptic technique by trained personnelSamples will be pseudo-anonymised, labelled with a unique study ID, and stored in the operating theatres department laboratory under NHS governanceAll processing will be performed within four hours of collection in accordance with TEG6s manufacturer guidelinesNo long-term storage, banking, or genetic analysis will be performed

#### 2.5.3. Clinical Outcomes and Follow-Up

Participants will be followed from preoperative baseline through twelve months postoperatively, capturing routine clinical outcomes including:Major adverse cardiovascular and cerebrovascular events, including myocardial infarction, stroke, and cardiovascular deathPostoperative bleeding, defined as Bleeding Academic Research Consortium type two or higherNeed for surgical re-exploration for haemostasisTransfusion requirements, including blood product administrationDuration of hospital stay, including intensive care unit and ward admissionWound healing and postoperative complications

Follow-up visits will occur at discharge between postoperative day five and seven, at six weeks postoperatively, at thirty days via telephone contact, and at twelve months through digital health records review.

### 2.6. Primary and Secondary Endpoints

#### 2.6.1. Primary Endpoint

The primary objective is to evaluate the association between perioperative platelet function test results and clinical outcomes in patients undergoing coronary artery bypass grafting.

#### 2.6.2. Secondary Endpoints

Prevalence of aspirin and clopidogrel resistance in the study populationDemographic and clinical predictors of antiplatelet resistance, such as age, sex, diabetes, renal function, body mass index, and surgical techniqueTemporal trends in platelet responsiveness from preoperative baseline through early and late postoperative periodsFeasibility of integrating PFT into perioperative care pathways to support individualized antiplatelet management in future trials

### 2.7. Statistical Analysis

#### 2.7.1. Baseline Characteristics and Study Flow

Baseline characteristics will be assessed to ensure comparability across participant groups. The following variables will be evaluated:Demographics: Age (continuous), sex (categorical), ethnicity (categorical), BMI (continuous)Clinical history: Diabetes status (categorical), renal function (eGFR, continuous), hypertension (categorical), previous PCI or MI (categorical)Operative details: On-pump vs. off-pump surgery (categorical), number of grafts (continuous), use of antiplatelet agents (categorical)

Continuous variables will be reported as means with standard deviations or medians with interquartile ranges, depending on data distribution. Categorical variables will be presented as frequencies and percentages. Group differences will be assessed using appropriate statistical tests:Student’s *t*-test or Mann–Whitney U test for continuous variablesChi-square or Fisher’s exact test for categorical variables

#### 2.7.2. Participant Flow Reporting

Patient enrollment and study completion rates will be documented using a CONSORT-style flow diagram, adapted for observational studies. The following parameters will be reported:Total number of eligible patients approachedNumber who consentedNumber excluded (with reasons)Number completing platelet function tests at each timepointNumber included in endpoint analysesNumber lost to follow-up at 6 weeks and 12 months

A study flow diagram will be included in publications, following recommendations from the STROBE statement for observational studies.

#### 2.7.3. Handling of Missing Data

Primary analyses will follow a complete case approach. If more than 10% of data is missing for a key variable, multiple imputation may be considered. All missing data patterns will be documented, and deviations will be reported in the final analysis.

#### 2.7.4. Primary Endpoint Analysis

The primary objective of this study is to evaluate the association between platelet function test results and clinical outcomes in patients undergoing elective and urgent CABG.

Summary Measures

Platelet function results will be summarized as mean ± standard deviation or median with interquartile range (IQR), depending on data distribution, for:AA channel (aspirin response)ADP channel (clopidogrel response)

Clinical outcomes, including MACCE, bleeding, re-exploration, and transfusion, will be reported as frequencies and proportions.

Method of Analysis

Correlation analysis: Pearson’s correlation for normally distributed data, Spearman’s rank correlation for non-parametric dataLogistic regressionEstimates the odds of postoperative events based on platelet resistance status (resistant vs. non-resistant)Adjusts for potential confounders (age, diabetes, renal function, surgical factors)Hierarchical data structure: Generalized estimating equations (GEE) or mixed-effects models will be used to account for repeated measures of platelet function over time.

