#### 2.1.3. Treatment and Rationale

As a non-interventional observational study, no study-specific treatment will be administered, and participants’ standard perioperative and postoperative care will remain unaltered.

All antiplatelet therapy will be prescribed at the discretion of the treating surgical teams, following institutional protocols and national guidelines. The study does not involve randomisation, dose escalation, or therapeutic modifications based on PFT results. Instead, it aims to evaluate the association between naturally occurring variability in platelet reactivity and clinical outcomes under standard care conditions.

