#### 2.1.4. Standard Medications Permitted

Patients undergoing elective and urgent CABG are expected to receive the following standard antiplatelet regimens:Aspirin (typically 300 mg within 6 h of return from operating theatre followed by 75 mg once daily)Clopidogrel (typically 75 mg once daily, when prescribed)

Additionally, concomitant medications—including beta-blockers, ACE inhibitors, statins, or anticoagulants (such as warfarin or direct oral anticoagulants, DOACs)—may be prescribed as per clinical indications. These will be recorded and accounted for in the final analysis as potential confounding variables affecting platelet function and surgical outcomes.

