#### 2.7.8. Secondary Endpoint Analysis

Analyses of secondary endpoints are exploratory and hypothesis-generating, as the study is not powered for statistical significance in these measures. Findings will guide future studies.

Variability in Platelet Function

Objective: Assess inter-individual variability in platelet inhibition across timepoints.Analysis:
Continuous values (% inhibition) summarized at baseline, discharge, and 6 weeksRepeated measures ANOVA or Friedman test for within-patient changesBoxplots and line graphs used for visualization

Prevalence of Platelet Resistance

Objective: Determine the proportion of patients with inadequate platelet inhibition.Analysis:
Categorical resistance status reported for each timepoint with 95% confidence intervalsChanges in resistance status analyzed using McNemar’s test for paired categorical data

Demographic and Clinical Predictors of Platelet Function

Objective: Explore associations between patient characteristics and platelet responsiveness.Analysis:
Univariable and multivariable linear regression for continuous % inhibition outcomesConsidered variables: age, sex, BMI, renal function, diabetes, and number of graftsSelection guided by clinical relevance and statistical significance (*p* < 0.1)

Impact of Platelet Resistance on Clinical Decision-Making

Objective: Evaluate whether platelet resistance influences treatment decisions, including DAPT use and discharge timing.Analysis:
Comparisons of DAPT prescription rates between resistant and non-resistant patients using chi-square or Fisher’s exact testLogistic regression to explore predictors of treatment decisions if data allows

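### The drugs that determine platelet inhibition and bleeding appear in no stated adjustment set, although the article says concomitant drugs will be accounted for as confounders

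*Protocol article*

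**What the plan says.** The primary analysis (section 2.7.4) is a logistic regression of postoperative events on resistant versus non-resistant status that "Adjusts for potential confounders (age, diabetes, renal function, surgical factors"). The same section summarises the "ADP channel (clopidogrel response") with no restriction to patients who take clopidogrel.

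Section 2.1.4 lists concomitant drugs that may be given, including "anticoagulants (such as warfarin or direct oral anticoagulants, DOACs"), and states: "These will be recorded and accounted for in the final analysis as potential confounding variables affecting platelet function and surgical outcomes".

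The antiplatelet regimen is not fixed. Section 2.1.3 says "All antiplatelet therapy will be prescribed at the discretion of the treating surgical teams"; section 2.1.4 lists "Clopidogrel (typically 75 mg once daily, when prescribed"); the inclusion criteria in section 2.4.1 accept aspirin or dual therapy. Regimen is collected in section 2.7.1 as "use of antiplatelet agents (categorical").

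Section 2.7.8 models percentage inhibition on age, sex, BMI, renal function, diabetes and number of grafts. Regimen appears in that section as something to be explained: "Comparisons of DAPT prescription rates between resistant and non-resistant patients".

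**The concern.** The exposure is a measure of drug effect. AA and ADP inhibition depend first on whether the patient is taking aspirin or clopidogrel and only then on how well the patient responds. If regimen is left out, a patient who was never given clopidogrel can count as clopidogrel-resistant, and the odds ratio compares prescribing groups as well as responders with non-responders. Surgical teams choose the regimen, so whatever led them to choose it may also bear on MACCE or bleeding.

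Anticoagulation raises a second problem. The article itself describes concomitant drugs as affecting both platelet function and outcome, then leaves them out of the list of adjusters. In the predictor model, a factor that only changes prescribing, diabetes for instance, could look like a factor that changes drug response. The study is meant to support later trials of tailored therapy, so an association of this kind would be carried forward.

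**Working it through.** The plan gives no figure on this point. The check is a comparison of sections followed by an illustration on assumed inputs.

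**Comparison of sections**

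| Variable | Stated role | In the 2.7.4 outcome model? | In the 2.7.8 inhibition model? |
|---|---|---|---|
| Oral anticoagulants and other concomitant drugs | Confounders to be accounted for (2.1.4) | Not named | Not named |
| Antiplatelet regimen | Discretionary (2.1.3), variable (2.1.4, 2.4.1), recorded (2.7.1) | Not named | Not named |

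For concomitant drugs, a commitment in one section is not carried into the model in another. For antiplatelet regimen, no commitment is broken; a recorded determinant of the exposure is left out.

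**Illustration 1: anticoagulation and bleeding, no true effect of ADP inhibition**

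All inputs are assumptions:
- anticoagulated, q = 10–30%
- clopidogrel given to cA = 10–20% of the anticoagulated and cN = 40–70% of the others
- bleeding risk bA = 25–30% and bN = 10%
- low ADP inhibition in u = 20–40% of clopidogrel takers and v = 80–90% of non-takers

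Formulas:
- LA = cA·u + (1 − cA)·v, and LN likewise with cN
- bleeding risk if ADP inhibition is low = [q·LA·bA + (1 − q)·LN·bN] / [q·LA + (1 − q)·LN]
- bleeding risk if not low: the same with 1 − LA and 1 − LN

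Central case (q = 20%, cA = 10%, cN = 50%):
- bA = 25%, u = 40%, v = 80%: LA = 0.76, LN = 0.60. Risks are 0.086/0.632 = 0.136 and 0.044/0.368 = 0.120. OR = 1.16.
- bA = 30%, u = 20%, v = 90%: LA = 0.83, LN = 0.55. Risks are 0.0938/0.606 = 0.155 and 0.0462/0.394 = 0.117. OR = 1.38.

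Over all corners of the ranges:
- lowest OR 1.05 (q = 10%, cA = 20%, cN = 40%, bA = 25%, u = 40%, v = 80%)
- highest OR 1.72 (q = 30%, cA = 10%, cN = 70%, bA = 30%, u = 20%, v = 90%)

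The true value is 1.0 throughout.

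**Illustration 2: regimen and any event, no true effect of resistance within regimen**

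Assumed inputs: 30–70% on clopidogrel; resistant on ADP in 40% of takers and 80–95% of non-takers; event risk between 5% and 15%, differing by regimen.
- Half on clopidogrel, 95% of non-takers resistant, risk 5% on and 15% off: (0.2×0.05 + 0.475×0.15)/0.675 = 0.120 against (0.3×0.05 + 0.025×0.15)/0.325 = 0.058. OR = 2.24.
- 30% on clopidogrel, 95% of non-takers resistant, risk 15% on and 5% off: (0.12×0.15 + 0.665×0.05)/0.785 = 0.065 against (0.18×0.15 + 0.035×0.05)/0.215 = 0.134. OR = 0.45.

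With regimen in the model, both return 1.00.

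**What the remedy costs in parameters**

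Exposure plus the four listed adjusters is at least 5 parameters; two drug indicators make at least 7. With 100 patients and an assumed event rate of 5–20% (5 to 20 events), events per parameter fall from 1.0–4.0 to 0.7–2.9.

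**The case against.** Five points can be made on the other side.

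**The lists may be shorthand.** Predictor lists differ across the article (sections 1, 2.7.8 and 3.3), and exact covariates are often left to an analysis plan. This holds in part. But section 2.7.4 gives its list without any sign that it is illustrative, and that list leaves out what section 2.1.4 undertakes to include.

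**Surgical factors might include regimen.** Section 2.7.1 files antiplatelet use under operative details. The text does not make that link for the model, and this reading cannot reach anticoagulants.

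**The prognostic question needs no drug adjustment.** Sections 1, 2.6.1 and 4 ask whether test results are associated with outcome and can stratify risk. For pure prediction this is fair. Section 2.1, however, asks about responsiveness to therapy, the exposure is called resistance, and section 2.1.4 itself calls drugs confounders.

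**The bias is small beside random error.** In the lower central case about 13 of 100 patients bleed (20%×25% + 80%×10%). With an assumed 60:40 split and OR 1.0, SE = √(1/7.8 + 1/5.2 + 1/52.2 + 1/34.8) = 0.61, so the 95% limits are about 0.30 to 3.3. This stands. But the bias, unlike random error, does not shrink in a larger follow-on study analysed the same way.

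**Events are too few for more terms.** This is a real constraint. It argues for choosing covariates by importance and for penalisation, not for leaving treatment out.

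A reader might also infer three stronger things that the documents do not support. The commitment in section 2.1.4 does not extend to antiplatelet regimen; its wording covers the concomitant drugs. Regimen is not used only descriptively, since section 2.7.8 tests dual-therapy rates by resistance status and may model treatment decisions. Nor can it be said that the bias for bleeding runs against the expected association: that needs anticoagulated patients to bleed more and to receive less clopidogrel, and the documents state neither.

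**Conclusion.** The point holds as an inconsistency for concomitant drugs, anticoagulants above all, and as an omission for antiplatelet regimen. As written, the primary odds ratio and the predictor coefficients can mix drug response with discretionary prescribing, most plainly on the ADP channel, where patients not on clopidogrel are not set apart.

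Confidence is high for what the text says and low for the size of the effect. The apparent odds ratios (1.05 to 1.72 in the first illustration, 0.45 to 2.24 in the second, truth 1.0) rest entirely on assumed prescribing and event rates. They show that the bias could be material and could go either way; they do not estimate it. It should be corrected before analysis. It is a structural risk to interpretation, not a demonstrated error in a result.

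**What to change.** 1. **Section 2.7.4.** Add two separate indicators to the adjustment set: P2Y12 inhibitor use at the time of the platelet test used as exposure, and oral anticoagulant use. For bleeding, take anticoagulation during the outcome period and before the event, with the window defined alike for patients with and without a bleed. Separate indicators are better than one combined regimen variable, because an anticoagulant category would pool patients with and without clopidogrel, and patients on no antiplatelet at baseline would have no category.
2. **Exposure.** Name which of the three tests in section 2.5.1 defines exposure for each outcome. Analyse ADP (clopidogrel) resistance only among clopidogrel takers at that test; the P2Y12 indicator then drops out of that analysis.
3. **Section 2.7.8.** Force P2Y12 inhibitor use and the other drug terms into the percentage-inhibition model, exempt from the p < 0.1 selection.
4. **Sparse events.** Use penalised regression (for example Firth) or drop a weaker covariate, named in advance. Report the bleeding association with anticoagulated patients excluded as a sensitivity analysis.
5. **Timing.** Use regimen at sampling, not regimen changed after the result, which may be a mediator. Section 2.1.2 (results blinded from the surgical team) and section 6 (results conveyed to the clinical team, who may modify treatment) must be reconciled, because they decide whether such changes can occur.

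Cost: mainly analysis wording, and one or two more parameters in a sparse model. Restricting the ADP analysis also shrinks it; at an assumed 30–70% on clopidogrel, 30 to 70 of 100 patients remain. The article says the drugs are recorded but not that they are recorded at each test, so the data collection form should be checked for that.

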#### 2.1.1. Overall Design

The study will be conducted at a single tertiary NHS cardiac surgery centre, enrolling 100 patients who will receive standard perioperative and postoperative care according to institutional and national guidelines. No study drug or investigational device will be tested. The study aims to generate real-world data that may inform future interventional trials or guideline updates regarding the role of PFT in optimizing antiplatelet therapy for surgical patients.

A formal sample size calculation was performed to ensure sufficient statistical power to detect meaningful variability in platelet function and its association with clinical outcomes. Assuming a moderate effect size (Cohen’s d = 0.5), a two-sided alpha level of 0.05, and 80% statistical power, the minimum required sample size for comparison of platelet function measures was estimated at 63 patients.

To account for an anticipated attrition rate of approximately 20%, due to loss to follow-up or incomplete PFT across multiple perioperative timepoints, the adjusted minimum sample size was calculated to be approximately 80 patients. To further enhance robustness and allow for exploratory subgroup and longitudinal analyses, a final target sample size of 100 patients was selected.

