## 3. Results

### 3.1. Participant Characteristics

Baseline demographic and clinical characteristics will be collected from enrolled participants to assess comparability between groups. Variables evaluated will include age, sex, ethnicity, body mass index, cardiovascular risk factors, preoperative medication use, and surgical approach.

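### Baseline haemoglobin and platelet count are known for every patient but are in neither the baseline variables nor the named confounders, so the transfusion and bleeding odds ratios may be confounded by them

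*Protocol article*

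**What the plan says.** Section 2.4.2 excludes patients with haemoglobin under 8 g/dL or platelets under 100 x 10^9/L at baseline. Both must be known before a patient is enrolled, and the cohort still contains all the variation above those limits.

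Section 2.7.1 lists the baseline variables. Besides demographics these are "Clinical history: Diabetes status (categorical), renal function (eGFR, continuous), hypertension (categorical), previous PCI or MI (categorical") and, for the operation, "On-pump vs. off-pump surgery (categorical), number of grafts (continuous), use of antiplatelet agents (categorical"). Section 3.1 gives a similar list: "age, sex, ethnicity, body mass index, cardiovascular risk factors, preoperative medication use, and surgical approach". Blood counts are in neither.

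Section 2.7.4 models the odds of postoperative events on resistance status and "Adjusts for potential confounders (age, diabetes, renal function, surgical factors"). On outcomes it says: "Clinical outcomes, including MACCE, bleeding, re-exploration, and transfusion, will be reported as frequencies and proportions".

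Section 2.1.4 widens the adjustment to concomitant medications: "These will be recorded and accounted for in the final analysis as potential confounding variables affecting platelet function and surgical outcomes". The subgroups (2.7.6) and the predictors of resistance (2.6.2, 2.7.8, 3.3) do not mention haemoglobin or platelet count either.

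**The concern.** The two values serve as an eligibility gate and are then dropped. Starting haemoglobin is an obvious candidate to predict who is transfused. Platelet count is a plausible predictor of bleeding, and plausibly also affects the result of a whole-blood platelet assay. Neither is a surgical factor in the ordinary sense, and renal function is at best a partial stand-in for haemoglobin.

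Two things are at stake. If either value differs between resistant and non-resistant patients, the odds ratio attributed to resistance partly reflects preoperative blood counts. If neither differs, omitting a strong predictor still costs some power. Section 2.7.9 puts the emphasis on effect sizes and confidence intervals, so a shifted point estimate matters even where no p-value crosses a threshold.

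**Working it through.** **Inputs from the article.** N = 80 to 100 and 38% resistant (the upper figure for aspirin in the Introduction). The lower N follows the plan's own step: 63/(1 - 0.20) = 78.75, so about 80, as stated in 2.1.1. The 63 itself comes from "Assuming a moderate effect size (Cohen’s d = 0.5), a two-sided alpha level of 0.05, and 80% statistical power" and is reproduced only as a number per group: 2 x (1.96 + 0.842)^2/0.5^2 = 62.8. That is a separate matter and does not enter here.

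**Inputs assumed, because the article gives none.** Event rate 10 to 50%. Odds of the event multiplied by 1.5 to 3 per SD lower haemoglobin. Haemoglobin lower in resistant patients by 0 to 0.5 SD. True odds ratio for resistance 1.

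**Step 1: size of the bias.** To a first approximation, crude OR = (OR per SD)^(difference in SD). For example, 2^0.25 = 1.19 and 1.5^0.5 = 1.22. Exact integration over a normal covariate gives:

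| Difference between groups | Crude OR when the true OR is 1 |
|---|---|
| 0 SD | 1.00 |
| 0.1 SD | 1.04 to 1.10 |
| 0.25 SD | 1.10 to 1.28 |
| 0.5 SD | 1.22 to 1.63 |

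**Step 2: simulation of the transfusion model.** Assumed: 30 to 40% transfused, OR 2.0 to 2.7 per SD of haemoglobin, and four unrelated covariates standing for the planned confounders. A correlation r between haemoglobin and the continuous assay value behind resistance status, split at 38%, means a group difference of 0.381/(0.38 x 0.62) x r = 1.62r SD. So r = 0.1, 0.2 and 0.4 correspond to 0.16, 0.32 and 0.65 SD. Positive r means lower haemoglobin in resistant patients.

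- Without haemoglobin, r = 0.1 gives a median OR of about 1.1, and r = 0.2 to 0.4 gives about 1.2 to 1.8. The false-positive rate at r = 0.2 to 0.4 is about 6 to 25%.
- With r = -0.3 the median OR is about 0.63 to 0.73.
- With haemoglobin in the model, the OR returns to about 1.0 and the error rate to about 4 to 7%.

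The approximation in step 1 agrees: 2.0^0.32 = 1.25, and 2.7^0.65 = 1.91 (slightly high at the extreme).

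**Step 3: no association.** With r = 0, a true OR of 3.5 and N = 80, adding haemoglobin raises power from 58% to 66% (OR 2.7 per SD) or from 66% to 69% (OR 2.0 per SD).

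**Step 4: what the extra terms cost.** Take five parameters for the planned model: resistance, age, diabetes, renal function and one surgical factor.

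| Event rate | Events at N = 80 to 100 | Events per parameter, 5 | With haemoglobin, 6 | With both, 7 |
|---|---|---|---|---|
| 10% | 8 to 10 | 1.6 to 2.0 | 1.3 to 1.7 | 1.1 to 1.4 |
| 30% | 24 to 30 | 4.8 to 6.0 | 4.0 to 5.0 | 3.4 to 4.3 |

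**Step 5: scale.** For a crude OR, the standard error of log OR is the square root of the sum of the reciprocals of the four cell counts. At N = 100 with 30% events this is sqrt(1/11.4 + 1/26.6 + 1/18.6 + 1/43.4) = 0.45, so the 95% interval runs a factor exp(1.96 x 0.45) = 2.4 each way. Over N = 80 to 100 and event rates of 10 to 50%, the factor is about 2.2 to 4.5.

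Only haemoglobin with transfusion was simulated in steps 2 and 3. No simulation was made for platelet count or for bleeding.

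**The case against.** A reader might infer that the primary odds ratios are confounded. The article does not support that. Confounding needs an association with resistance as well as with the outcome, and no section links either blood count to the TEG6s result. If there is no such link, the bias is nil.

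A reader might also take transfusion as a primary outcome. Section 2.7.4 names it, but the Introduction, 2.1 and 3.2 give MACCE, bleeding and re-exploration, and the Introduction places transfusion under a secondary objective. Bleeding is the clearly primary part of this point, and it has no simulated magnitude.

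Other objections stand in part:

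- The simulation treats the planned confounders as unrelated to haemoglobin. Age or renal function may already carry some of its information, so the residual bias could be smaller.
- The confidence interval is wider than the bias over most of the range.
- With no association, the model without haemoglobin estimates a different, less conditional odds ratio (non-collapsibility). It is not a biased estimate of the same one, so only the modest power loss counts.
- The rate of BARC type 2 or higher bleeding is not given, so two more terms could overfit that model.

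The objection that covariate lists belong in a fuller document carries less weight. Section 2.7.1 enumerates its variables and 2.7.4 names its confounders. Section 2.1.4 shows that the second list is not closed, but it adds only medications.

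**Conclusion.** The point holds as a possible confounding and a modest loss of precision. Two baseline values that must exist for every patient are left out of both named lists, although both plausibly bear on transfusion or bleeding. For transfusion, a true odds ratio of 1 could read as about 1.0 to 1.8, or as about 0.63 to 0.73 if the association is reversed at a correlation of -0.3. With no association, the loss is about 3 to 8 points of power at an assumed odds ratio of 3.5. All of this rests on assumed event rates, haemoglobin effects and correlations. For bleeding, and for platelet count, the direction of the argument is the same but its size is not established. The point does not touch the MACCE or re-exploration results.

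**What to change.** - In 2.7.1, add baseline haemoglobin (g/dL) and platelet count (10^9/L), both continuous, to the baseline variables, so that any imbalance by resistance status can be seen.
- In 2.7.4, add baseline haemoglobin, continuous, to the adjustment set of the transfusion model.
- For bleeding, keep the planned model and prespecify a sensitivity analysis that also adjusts for haemoglobin and platelet count, using penalised fitting (for example Firth) if events are few.
- Leave the MACCE and re-exploration models unchanged.

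No new measurement is needed, and the text change is a sentence or two in each section. The cost is one more term for transfusion and two for the bleeding sensitivity analysis, in models that already have few events per parameter. Fixing this before the data are seen also avoids choosing covariates by their results.

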#### 2.7.6. Predefined Subgroup Analyses

Subgroup analyses will explore variations in platelet function and clinical outcomes by:Diabetes status (yes/no)Age groupRenal functionClopidogrel vs. aspirin resistanceSex (male vs. female)

Interaction terms in regression models will be used to evaluate subgroup effects.

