### 3.2. Platelet Function and Clinical Outcomes

Platelet function test results will be analyzed at three timepoints: preoperative baseline, postoperative discharge, and six-week follow-up. The degree of platelet inhibition will be reported as percentage inhibition in response to arachidonic acid and adenosine diphosphate pathways, reflecting aspirin and clopidogrel effectiveness, respectively.

The prevalence of aspirin and clopidogrel resistance in the study population will be determined based on predefined cutoff values from the TEG6s Platelet Mapping system. Differences in platelet responsiveness between groups will be evaluated using repeated measures analysis of variance or non-parametric alternatives, depending on data distribution.

The primary analysis will assess correlations between platelet function test results and major adverse cardiovascular and cerebrovascular events, including myocardial infarction, stroke, cardiovascular death, postoperative bleeding complications, and the need for surgical re-exploration. Univariate correlations will be explored using Pearson or Spearman correlation coefficients, while logistic regression models will estimate the odds ratios for adverse outcomes associated with platelet resistance.

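### For rare outcomes such as MACCE, the adjusted logistic model in 2.7.4 will often be inestimable, and it dichotomises an exposure measured as continuous % inhibition

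*Protocol article*

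**What the plan says.** Section 2.7.4 of the protocol article gives two routes from platelet function to outcome. The first is correlation, which section 3.2 describes as unadjusted: "Univariate correlations will be explored using Pearson or Spearman correlation coefficients". The second is logistic regression, which estimates "the odds of postoperative events based on platelet resistance status (resistant vs. non-resistant") and adjusts for "potential confounders (age, diabetes, renal function, surgical factors"). Section 3.2 repeats that split: "Univariate correlations will be explored using Pearson or Spearman correlation coefficients, while logistic regression models will estimate the odds ratios".

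The number of surgical factors is not given. Section 2.7.1 lists two candidates: "On-pump vs. off-pump surgery (categorical), number of grafts (continuous"). Section 2.1.4 adds concomitant medication: "These will be recorded and accounted for in the final analysis as potential confounding variables affecting platelet function and surgical outcomes".

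The outcomes are several: "Clinical outcomes, including MACCE, bleeding, re-exploration, and transfusion, will be reported as frequencies and proportions". No expected rate is stated for any of them. Enrolment is 100, with attrition of about 20% (2.1.1), and the primary analyses use complete cases (2.7.3, 2.7.5, 2.7.7).

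Interactions belong to the subgroup section, 2.7.6: "Interaction terms in regression models will be used to evaluate subgroup effects". One of the five listed subgroups contrasts clopidogrel resistance with aspirin resistance.

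**The concern.** MACCE is defined narrowly as MI, stroke or cardiovascular death. In 80-100 patients it may occur only a few times. A logistic model with five or more terms then has about one or two events per term. With so few events, some combination of covariates often separates events from non-events. The maximum-likelihood odds ratio is then infinite or undefined. When the model does converge, its intervals are very wide. Section 2.7.9 puts its emphasis on effect sizes and confidence intervals, which is what such a model cannot supply. If it fails, the replacement would be chosen after the outcomes have been seen.

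The second loss is avoidable. Percentage inhibition is already collected and, in 2.7.8, already modelled as continuous. Only the adjusted outcome model cuts it to yes or no, in a study with little information to spare.

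**Working it through.** **The plan's own figures.** The article has no event-based calculation to reproduce. Its sample size rests on d = 0.5, two-sided 5%, 80% power: 2 x (1.96 + 0.8416)^2 / 0.5^2 = 62.8, so 63. That is a per-group number, which is a separate matter. Attrition: 63 / 0.8 = 78.75, about 80. Neither figure involves event counts or model terms.

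**Inputs.**
- Patients: 100 enrolled (2.1.1); 100 x 0.8 = 80 complete cases at 20% attrition.
- Terms: resistance, age, diabetes, renal function and one surgical factor = 5; with both operative factors in 2.7.1 = 6.
- Resistance prevalence: 38% (Introduction, an upper limit for aspirin; 40% for clopidogrel).
- Assumed, not in the article: event rates of 2-40%, diabetes 35%, off-pump 20%, no true effects.

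**Estimability.** For each simulated data set, a linear program checked whether any linear combination of the terms separates events from non-events (400 data sets per setting). The five-term model uses on/off-pump as its surgical factor.

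| Event rate | N = 80: expected events; events per term (6) | Separated, 5 / 6 terms | N = 100: expected events; events per term (6) | Separated, 5 / 6 terms |
|---|---|---|---|---|
| 5% | 4; 0.67 | 65% / 63% | 5; 0.83 | 53% / 52% |
| 10% | 8; 1.33 | 27% / 27% | 10; 1.67 | 16% / 19% |
| 15% | 12; 2.0 | 10% / 9% | 15; 2.5 | 5% / 4% |
| 20% | 16; 2.67 | 4% / 5% | 20; 3.33 | 1% / 3% |
| 30% | 24; 4.0 | <1% / <1% | 30; 5.0 | <1% / <1% |

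Other runs gave 54-60% at 5% and 12-30% at 10%. A rerun with 1,500 data sets per setting gave 52-64%, 17-27% and 5-11% at 5, 10 and 15%. Much of the separation comes from the binary covariates. In the same rerun, number of grafts as the only surgical factor gave 30-42% at 5% and 4-11% at 10%.

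One resistance-by-diabetes interaction added to six terms gives 87-89% at 5% and 46-57% at 10%.

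**Dichotomisation.** For a normal exposure with a small linear-logit effect, the fraction of information kept is phi(z_p)^2 / [p(1 - p)].
- p = 0.38: 0.3808^2 / 0.2356 = 0.615, loss 38%.
- p = 0.40: 0.3863^2 / 0.24 = 0.622, loss 38%.
- p = 0.30: 0.3477^2 / 0.21 = 0.576, loss 42%.
- p = 0.20: 0.2800^2 / 0.16 = 0.490, loss 51%.

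Bounded, beta-shaped exposures cut at 38% lost about 22-33%.

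**What each part of a remedy does.** Making the exposure continuous while keeping six terms barely helps at 5% events: 60% against 63% (N = 80) and 45% against 52% (N = 100). Continuous exposure plus one continuous score brings separation to about 1-3% at 5% events. Much of that is data sets with no event at all: 0.95^80 = 1.7%, 0.95^100 = 0.6%. Firth estimates existed in 98.5-100% of six-term runs (N = 80). Their median 95% intervals still spanned about 90-, 26- and 15-fold at 5, 10 and 15% events, against 80-, 28- and 17-fold for maximum likelihood where it converged.

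**The case against.** A reader might infer that the whole primary analysis cannot be estimated. The article does not support that. It gives no event rate, and the logistic model also serves bleeding and transfusion. At 15-20% events separation is about 10% or less, and at 30% below 1%.

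A reader might also infer that the primary model carries the interactions. It does not; they are confined to the exploratory subgroups in 2.7.6.

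Nor does the primary analysis as a whole throw away 38% of the exposure information. The correlations use the continuous values, so the loss applies to the adjusted logistic part, and its size depends on distribution and prevalence. A Pearson coefficient against a yes/no outcome is not invalid (it is equivalent to a t-test), but it is unadjusted and gives no risk estimate.

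A condensed article may leave the estimation method and the covariate list per outcome to an analysis plan, so maximum likelihood is an inference from the bare name of the method. That is fair, and silence on penalisation is not itself the fault. What stands is what the article does fix: a binary exposure and at least five terms for every outcome, whatever its frequency.

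Finally, the root cause is too few events for the sample size, which model wording cannot cure. That also stands. A better model can be fitted and read honestly, but it will not be precise.

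**Conclusion.** The point holds for rare outcomes. If MACCE (or re-exploration) occurs in about 5% of patients, the stated adjusted model fitted by maximum likelihood is inestimable in roughly 50-65% of data sets; at 10% in about 12-30%; at 15% in about 10% at most. These figures assume 80-100 analysed patients, 38% resistance, 35% diabetes and 20% off-pump surgery among the covariates. They are lower if the only surgical factor is number of grafts. The problem is not shown for commoner outcomes such as BARC 2+ bleeding or transfusion.

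The adjusted model also gives up about 38% of the exposure information at 38-40% prevalence under normality. The loss is larger if resistance is less common than those upper limits, and possibly smaller for a bounded, non-normal distribution.

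This should be changed before outcomes are examined. It does not invalidate the study.

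**What to change.** In 2.7.4:
- Make continuous % inhibition the exposure in the adjusted outcome model, reported as an odds ratio per 10 percentage points. Keep resistant versus non-resistant as secondary.
- For rare outcomes, use Firth-penalised logistic regression with profile-likelihood intervals.
- For those outcomes, replace the separate covariates by one prespecified summary score not fitted to the same few events (for example an existing preoperative risk score), or by one or two fixed covariates.
- Do not rely on the correlation coefficients as risk estimates.

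In 2.7.6:
- Fit no interaction terms for rare binary outcomes.
- Do not treat the clopidogrel-versus-aspirin resistance contrast as an effect modifier, because it is the exposure itself.

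All three parts of the change to 2.7.4 are needed: a continuous exposure alone barely reduces separation, and Firth alone leaves the intervals as wide as before.

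The cost is wording and standard software; no new data are needed. The price is slight shrinkage, a less familiar odds ratio and coarser control of confounding. Intervals for MACCE will stay wide, and the plan should say so.
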